## Methods/Design

### Study design and objectives

This is a prospective pagoda (community)-based cohort study with the following primary objectives: (i) to determine the seroprevalence of antibodies indicating previous *Aedes*-transmitted DENV infection in children; and (ii) to describe the seropositivity to *Aedes* salivary gland homogenate (Table 1). The study will screen up to 1200 and recruit up to 771 children aged 2–9 years for study enrollment and then follow them longitudinally for three years. The study is being conducted over three years given the high rate of variability in *Aedes*-transmitted disease transmission from year to year. The study is focused on children aged 2–9 years of age as they have the greatest burden of disease in Cambodia and thus offers comparability to other pediatric DENV cohorts [23–25, 27].

**Table 1 Tab1:** Study objectives and endpoints

Objectives	Endpoints	Justification for endpoints
• Primary		
Describe the seroprevalence of dengue infection (both symptomatic and inapparent) in children aged 2–9 years-old in Kampong Speu	Prevalence of symptomatic and inapparent dengue infection (serotypes 1–4) as detected semiannually *via* ELISA (binary outcome present/absent) over a 3-year period in Kampong Speu in children aged 2–9 years-old	Detailed knowledge of dengue seroprevalence and transmission season variability will help establish an epidemiological foundation to prepare for larger future studies such as disease incidence studies or vector interventional trials
Describe the seroprevalence of reactivity to *Ae. aegypti* salivary gland proteins in children aged 2–9 years-old in Kampong Speu	Prevalence of *Ae. aegypti* salivary gland homogenate reactivity as detected by ELISA assay (binary outcome present/absent) during wet and dry seasons over a 3-year period in Kampong Speu in children aged 2–9 years-old	Characterizing the *Ae. aegypti* salivary protein reactivity profile in Cambodians is the first step prior to assessing how *Ae. aegypti* saliva exposure modulates disease in humans
• Secondary		
Describe epidemiology of symptomatic *Aedes*-transmitted infections in a Cambodian pediatric population	Positive RT-PCR result for diagnosis of dengue, chikungunya, and Zika viruses (or IgM capture ELISAs for dengue as needed)	Dengue is the predominant flavivirus, but other circulating arboviruses complicate the serologic diagnosis of prior immunity and it will be important to characterize this burden given the ease and little cost added to run the multiplex RT-PCR compared to a DENV RT-PCR alone
Establish and characterize spatial relationships between population abundance of *Ae. aegypti* (through entomological indicators), magnitude of human antibody response to *Ae. aegypti* mosquito saliva, and disease development	Geographical information system with all data components (mosquito catch sites, houses, schools) referenced by latitude and longitude in addition to a series of map layers (point maps, smoothed maps) to evaluate relationships between IgG intensity of human antibody response (ΔOD per ELISA) to *Ae. aegypti* salivary homogenate, entomological indices (e.g. House index defined as larvae present per 100 houses surveyed), and disease development	These data and analyses will allow for detailed spatio-temporal analysis of the data at individual, house and community levels. Similar published methods (except different entomological indices) were used for assessment of *Anopheles* salivary protein exposure at the Thai-Burma border for risk of malaria transmission [53]
Characterize temporal dynamics of human antibody reactivity to *Ae. aegypti* salivary gland homogenate	Seroconversion to *Ae. aegypti* salivary homogenate in relationship to season (wet *versus* dry) and collected time-dependent variables defined as mean and maximum rainfall, temperature and humidity	The natural time course of salivary protein exposure, particularly in confirmed arboviral disease settings, has not been well characterized. Retrospective repeat analyses of non-diseased samples have suggested that salivary IgG antibodies may last 30–40 days or possibly up to 4 months [18]. Seasonal variation and climate factors are implicated in both disease transmission and vector abundance [54, 55]. Quantifying vector-host interaction at the individual level in the context of more global factors is necessary to further understanding saliva immunity, disease transmission, and outbreak model prediction
Identify specific immunodominant molecules in *Ae. aegypti* saliva for functional characterization	Western blot analysis of sera from participants with strongest ELISA positivity to *Ae. aegypti* whole salivary gland homogenate compared to *Anopheles* and *Culex* to assess cross-reactive immunogenicity to mosquito saliva *versus* specific *Aedes* markers	This next layer of analysis to identify specific immune-dominant molecules, from a whole-protein approach, will provide the highest probability of identifying novel proteins, irrespective of immune-modulatory function, that can then be characterized. It is essential to assess reactivity to the saliva of *Anopheles* and *Culex* in order to exclude cross-reactive antigens and select for *Aedes*-specific markers
Characterize wild-caught *Aedes* sialotranscriptomes (transcriptomes of mosquito salivary glands) and midgut composition	Capture a minimum of 25 female *Ae. aegypti* mosquitos for transcriptional comparison to LMVR-reared *Ae. aegypti* mosquitos	Wild-caught *Ae. aegypti* may harbor considerable difference to inbred mosquito strains maintained in insectaries. Differences in salivary and midgut composition may help explain unique vector competence aspects and immunogenicity of the strains of *Ae. aegypti* in Cambodia
• Tertiary/Exploratory		
Investigate a relationship between the magnitude of human antibody response to *Aedes* salivary gland homogenate to subsequent disease development to *Aedes*-transmitted disease	Correlate the incidence of *Aedes*-transmitted arboviral infection (as defined below) with seroconversion to *Ae. aegypti* salivary homogenate	Retrospective human studies have identified seropositivity to *Ae. aegypti* proteins proving that humans mount antibody responses to specific *Ae. aegypti* salivary proteins [17–19, 40]. Mice studies demonstrate *Ae. aegypti* salivary protein immunization as protective of disease whereas co-inoculation of virus with saliva worsens disease
Characterize the presence and types of alpha-thalassemia variants in the Cambodian population	Presence or absence of alpha thalassemia as determined by genotyping of alpha globin deletions and variants in cohort participants and targeted sequencing of these candidate genes	Dengue-infected patients with alpha thalassemia clinically present differently than patients without erythrocyte variants [49, 50]. In *vitro* studies have also shown that cells derived from thalassemia trait carriers have reduced susceptibility to DENV infection. Describing the presence of alpha-thalassemia in the Cambodian population as well as the associated alpha globin deletions will be important for future studies to investigate the link between alpha thalassemia and arboviral disease development
Characterize pattern of *Aedes* salivary reactivity and cellular immune responses to saliva across baseline, final, acute and convalescent time points of *Aedes*-transmitted disease	Evaluation of the cellular immune response to *Aedes* whole salivary gland homogenate (e.g. assess T-cell activation or cytokine production by vector saliva) in participants at baseline, final study visit, and time points after with RT-PCR-confirmed infection with DENV, CHIKV, or ZIKV	Understanding cellular immunity to *Aedes* saliva will inform vaccine design. An ultimate aim of identifying a small peptide antigen in *Aedes* saliva would be its use as an adjuvant in conjunction with an arboviral-specific antigen for vaccine development

Twice per year, during dry (March) and wet (August) seasons, participants come to their local pagoda, a community temple, to provide blood samples for tests of seroconversion after DENV infection and to characterize their *Aedes* salivary protein seroconversion profiles (Table 2). At any time of year, febrile children are referred to the district hospital where putative cases of febrile *Aedes*-transmitted arbovirus infections can be identified by symptoms (e.g. fever, myalgias, headache, rash). For febrile cases with positive rapid diagnostic tests or for those with a high index of clinical suspicion, confirmatory tests of viral shedding of DENV, CHIKV or ZIKV virus are performed *via* RT-PCR.

**Table 2 Tab2:** Schedule of activities

Procedure	Screen and enroll	Dry ± 28 days	Wet ± 28 days	Dry ± 28 days	Wet ± 28 days	Dry ± 28 days	Wet ± 28 days	Febrile sick visit ± 2 days	Convalescent visit Day 7 ± 2 days	Convalescent visit Day 28 ± 4 days
Informed consent	×									
Demographics	×									
Baseline medical history questionnaire	×									
Baseline physical exam	×									
Interval exam and questionnaire		×	×	×	×	×	×			
Concomitant medication review	×	×	×	×	×	×	×	×	×	×
Sick visit exam (with height and weight) and questionnaire								×		
Convalescent exam and questionnaire									×	×
Height and weight	×						×	×		
Vital signs	×	×	×	×	×	×	×	×	×	×
Dengue rapid diagnostic test (RDT)								×		
RT-PCR multiplex for acute arboviral diagnosis								× (if RDT+)		
Sera collection for ELISAs	×	×	×	×	×	×	×	× (if RDT+)	×	
Hemoglobin		×								
Alpha-thalassemia screening		×								
Peripheral blood mononuclear cells	×						×	× (if RDT+)		×
Complete case report forms	×	×	×	×	×	×	×	×	×	×

*Note*: Dry seasons visits take place every March whereas wet season visit take place every August

To reduce bias from loss to follow-up, the study team enrolls volunteers who are located within 5.5 km of the district hospital, will do follow-up sampling in the community, and will provide incentives commensurate with the previous studies approved by the Cambodian ethics committee.

### Study population and site

The study is carried out in Chbar Mon town, a peri-urban area with an estimated population approximately 60,000 located 44 km west of Phnom Penh city center (Fig. 1). Over 2000 primary school students who reside in 4 km^2^ area of the three easternmost and populous communes. This area includes a comparable but unconfirmed number of children aged 0–6 years old who have yet to enter school. Inclusion and exclusion criteria are listed in Table 3.

**Fig. 1 Fig1:**
[figure not shown]
Primary study area. The inset map (bottom right) indicates the location of Chbar Mon town, Kampong Speu (red cross) in Cambodia. The main map indicates the study area (with a green outline) and recruitment sites (green triangles) where participants are recruited for immunological indicators of mosquito exposure

**Table 3 Tab3:** Study eligibility criteria

Inclusion criteria	Exclusion criteria
(i) Provision of signed and dated informed consent form	(i) Current or prior use of immunosuppression in the previous six months
(ii) Stated willingness to comply with all study procedures and availability for the duration of the study	(ii) Treatment with an investigational drug or vaccine in previous six months
(iii) Male or female, aged 2–9 years	(iii) Any event or information deemed unsafe at the discretion of the principal investigator
(iv) Live within approximately 5.5 km of the Kampong Speu Referral hospital;	
(v) In good general health evidenced by medical history	
(vi) Willing to allow biological samples to be stored for future research	

National Dengue Control Programme data indicate that Kampong Speu is one of the higher burden provinces with a cumulative incidence of approximately 50 per 100,000 persons (over last three years based on 2013 census data). This number was similar to the national programme’s estimation of cumulative incidence in Kampong Cham, where rates of laboratory-confirmed cases ranged from 25 to 100 per 100,000 persons in 2015–2017 (unpublished national programme data).

### Community engagement

Engaging community stakeholders is critical to the success of a community-based cohort in Cambodia and is the basis of the effective collaboration between the National Dengue Control Programme, the provincial health departments, and the National Institute of Allergy and Infectious Diseases (NIAID) in conjunction with the Cambodian National Center for Parasitology, Entomology, and Malaria and Control (CNM). Chbar Mon is the largest Ministry of Health operational district in Kampong Speu Province and is the site of the Kampong Speu District Referral hospital, a hospital of approximately 100 beds with 130 staff of medical doctors, nurses and lab technicians. At this hospital, DENV fever is often clinically diagnosed (or sometimes confirmed by a SD Bioline Dengue Duo NS1/IgG/IgM rapid test when available) and reported to the National Dengue Control Programme, but the hospital does not serve as one of the five RT-PCR-confirmed dengue sentinel surveillance sites. Given its proximity to Phnom Penh, samples will be transported to the CNM laboratory for RT-PCR processing.

Four months prior to study start, a community engagement team (including the dengue provincial supervisor) was established and briefed on the overall objectives of the study along with the provincial clinical staff, including three pediatric specialist physicians who see patients in both the private and public sector clinics in Chbar Mon. The community engagement team then met with multiple village chiefs and their villagers across the three easternmost subcommunes of Chbar Mon for information sessions regarding the study. The community engagement team, in conjunction with the village chiefs and local monks, developed a recruitment schedule based on the availability of various community pagodas across Chbar Mon town. An estimated 97% of Cambodians are Buddhist and there are no other major enclaves of other religious groups in Chbar Mon, meaning that the use of pagodas is appropriate to gather a representative sample [28]. To enroll a wide variety of ages and villages within the Chbar Mon town, a different pagoda is designated for recruitment each week during the three-month enrollment period. Cohort enrollment will be structured for four age quadrants: 2–3 years of age, 4–5 years of age, 6–7 years of age, 8–9 years of age with the goal of approximately 192 children in each.

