### Statistical analysis

The primary endpoints will be defined as:(i)Seropositivity to DENV1-4 per indirect IgG ELISA (with plaque reduction neutralization assays performed as necessary to confirm inapparent dengue infections)(ii)Seropositivity to *Ae. aegypti* salivary gland homogenate

Seroprevalence to each dengue serotype will be presented as a proportion for each timepoint. Unadjusted and adjusted logistic regression models will be performed evaluating the relationship between time and seroprevalence, with adjustments for age, year or season of collection, and socio-economic conditions (e.g. type of housing). Further, the seroconversion rate and change in the immune status will be determined by participants and separated by age group during the study period. Quasi-Poisson regression models will be fit to evaluate the relationship of age, year, socio-economic conditions (e.g. type of housing) to the primary endpoints of dengue infection or *Ae. aegypti* salivary gland homogenate seropositivity and to estimate prevalence ratios.

Because seroconversion to *Ae. aegypti* salivary gland homogenate is measured repeatedly on subjects over three years during wet and dry season, a single subject may be negative for seroconversion at one time, and positive at a later time. This will allow us to perform our secondary objective to evaluate the kinetics of the antibody response. Given these changing values, seroprevalence to *Ae. aegypti* salivary gland homogenate will be presented as proportion representing point prevalence for each season in each year of the study.

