We will perform regression models (logistic for dichotomy predictors, quasi-Poisson models for incidence rates, linear models or mixed models for continuous predictors), to investigate the effect of environmental and socio-demographic conditions on the prevalence of *Aedes* salivary protein seroconversion (e.g. age, type of housing, number of domestic water containers) and season-specific data such a humidity, temperature and rainfall. All data will be geographically referenced. To evaluate spatial or temporal aggregation of salivary gland seroconversion, space-time scan statistics will be used. Exploratory spatial analyses will look for statistical clustering of disease, of IgG response and of mosquito abundance using both global and local indicators of spatial autocorrelation [33]. Smoothed heat maps will be created using QGIS software (https://www.qgis.org/en/site/). Spatial data will then be used to estimate risk factors for strongly positive antibody response to *Ae. aegypti* saliva and to risk of disease using generalized linear regression or generalized additive models (quasi-Poisson and logistic regression models), where appropriate.

The difference between groups in continuous secondary/exploratory outcomes will be tested by nonparametric Wilcoxon rank sum test, or if inferences on differences in means are desired, using a 2-sample t-test [34]. To test for differences among more than two groups, either a Kruskal-Wallis rank test (for nonparametric inferences) or a one-way ANOVA (for inferences on the means) will be used to test for overall differences. An appropriate data transformation (e.g. log_10_-transformation) may be applied to make inferences on ratios of geometrics means or to better satisfy assumptions of symmetry and homoscedasticity (similar variance).

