Exploratory analyses for the relationship of *Ae. aegypti* saliva seroconversion with disease development will model the rate of incidence of composite *Aedes*-transmitted arboviral disease (as defined above) using a quasi-Poisson model. The primary interest will be in the relative risk (RR) of infection comparing at risk subjects with seroconversion to *Ae. aegypti* salivary protein to those without seroconversion at that time. Exposed will be defined as those with seroconversion to specific *Ae. aegypti* salivary protein while unexposed will be those without reactivity at baseline and each follow-up time point. For this analysis, seroconversion will be defined as a binary variable (present/absent) based on the level of antibody to *Ae. aegypti* salivary gland homogenate (positivity is generally considered two standard deviations above the mean optical density value for negative controls as determined by an ELISA assay with further adjustment as needed to account for cross-reactivity to *Anopheles* or *Culex* saliva).

To compare the rates in secondary/exploratory outcomes for significant differences in arboviral infection between participants with or without evidence of salivary protein exposures or to examine other groups such as alpha thalassemia variants, we will use quasi-Poisson models and central Fisher’s exact tests. As previously stated, secondary and exploratory analyses will evaluate ELISA values as background (negative), low, medium and high quartiles, based on range and as a continuous variable. From the subset of samples with the highest positive values from both primary and secondary analyses, Western blot assays will be used to identify the most immunodominant protein candidates for functional characterization and future studies on epitope identification and characterization. Western blot assays will also be run against *Culex* and *Anopheles* saliva to account for cross-reactive immunogenicity to mosquito saliva in general.

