Retrospective studies of human sera have demonstrated the usefulness of anti-*Aedes* salivary gland extract as: (i) a marker of *Aedes* exposure; and (ii) a general corollary of dengue transmission potential [17–19, 40, 41]. In studies in Colombia and France, it has been shown that anti-*Aedes* saliva antibodies can last at least 40 days and possibly up to 4 months [18, 42]. In Colombia, retrospective analysis of febrile patient sera demonstrated that IgG antibodies to whole *Ae. aegypti* salivary gland extract were significantly higher in DENV-viremic patients compared to non-infected controls, serving as a marker of vector exposure [18]. Studies have shown that IgG antibodies to SGE are more specific than IgM antibodies with less cross-reactivity to other mosquito vector species like *Culex* spp., but overall, *Culex* and *Aedes* appear to have species-specific saliva reactivity in terms of human antibody response given that they diverged over 55 million years ago [17, 42]. There is little cross-reactivity in the *Anopheles* genera that diverged more than 150 million years ago from *Aedes* [43]. While these studies on markers of exposure laid the groundwork for anti-*Aedes* antibody identification and assay development, they have yet to contribute to our understanding of saliva-mediated pathogenesis of arboviral disease in humans.

There is only one retrospective study published from Thailand evaluating the correlation of MSP antibodies to arboviral disease severity [19]. In this serosurvey of 101 paired samples, hospitalized Thai children with acute primary or secondary dengue infection demonstrated higher total IgG antibodies to total *Ae. aegypti* salivary gland extract compared to uninfected hospitalized controls, suggesting higher exposure to the vector correlated to higher risk of infection. However, of the three immunogenic saliva *Ae. aegypti* proteins identified in the study, there was no uniform expression pattern of antibody response magnitude to correlate to disease severity [19]. The lack of baseline samples and the cross-sectional retrospective nature of the study limited its conclusions. There are no published prospective studies of human antibody response to mosquito saliva in regards to arboviral disease development or pathogenesis.

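### Enrolment ties each calendar week to a different pagoda, so location and time are largely confounded in the enrolment round and seasonal drift in saliva reactivity can look like spatial clustering

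*Protocol article*

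**What the plan says.** **Recruitment.** Under Community engagement, the article says that "a different pagoda is designated for recruitment each week during the three-month enrollment period". The team, with village chiefs and monks, "developed a recruitment schedule based on the availability of various community pagodas across Chbar Mon town". The order was therefore set by convenience and not randomised.

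**The antibody.** Table 1 reports that "salivary IgG antibodies may last 30–40 days or possibly up to 4 months". The Discussion says that such antibodies "can last at least 40 days and possibly up to 4 months". Table 1 adds: "Seasonal variation and climate factors are implicated in both disease transmission and vector abundance".

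**Use of the data.** Table 2 collects serum for ELISA at enrolment and at six later rounds, in March and August, each with a window of ±28 days. The exploratory disease analysis uses baseline saliva status ("unexposed will be those without reactivity at baseline and each follow-up time point"). Under Statistical analysis, "To evaluate spatial or temporal aggregation of salivary gland seroconversion, space-time scan statistics will be used", and global and local spatial autocorrelation of the IgG response is also planned. Mapping IgG intensity against mosquito indices and disease is a secondary objective.

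**Time terms.** The seroprevalence models adjust for year or season. The saliva regressions add season-specific humidity, temperature and rainfall. No term for week or date of draw is stated for the clustering analyses.

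**The concern.** If each recruitment week has its own pagoda, a comparison of neighbourhoods at enrolment is also a comparison of weeks. That would do little harm for a stable marker. Saliva IgG is described as possibly short-lived relative to a three-month enrolment, and as a response to a vector whose abundance is seasonal. Children drawn in the first and last weeks may therefore reflect different exposure periods, wherever they live.

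The planned year or season term does not help, because it is constant or nearly so within the enrolment period. In enrolment data alone, a space-time scan cannot tell a purely temporal rise from a local cluster, because each week contributes one location. This is a bias, so neither a larger sample nor a design effect for clustering removes it.

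At stake are the saliva hot-spot maps and the relation of IgG intensity to mosquito abundance and disease.

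**Working it through.** The article gives no figure for this confounding, so there is none to reproduce. The one figure taken from its sample-size section is the enrolment target: 701 × 1.10 = 771.1, stated as 771.

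**Inputs from the article:** 771 children; three months of weekly recruitment; persistence of 30–40 days, possibly up to 4 months; follow-up windows of ±28 days.

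**Assumptions:** 13 weeks and 13 pagodas, one per week; equal numbers; no true spatial difference; SGH seroprevalence drifting linearly with calendar week; pagodas placed at random in a 2 × 2 km area. The article gives neither the number of pagodas nor the size of any drift.

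**Step 1, children per pagoda-week.** 771/13 = 59.3, taken as 59.

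**Step 2, can reactivity change within enrolment?** Treat the persistence figures as half-lives (an assumption). The share of a response left after 12 weeks (84 days) is 0.5^(84/h):
- h = 30 days: 0.5^2.8 = 14%
- h = 40 days: 0.5^2.1 = 23%
- h = 120 days: 0.5^0.7 = 62%

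Material change is possible at the lower figures and much damped at the upper one. Over the 56-day span of a follow-up window the shares are 27%, 38% and 72%.

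**Step 3, false differences between pagodas.** For a Pearson chi-square on a 13 × 2 table (12 df), a total drift D centred on 0.50 gives approximate noncentrality λ = 59 × D² × Σ(k/12 − 0.5)² / 0.25, with k = 0 to 12 and the sum equal to 182/144 = 1.264.
- D = 0.10: λ = 59 × 0.01 × 1.264 / 0.25 = 2.98, rejection about 15%
- D = 0.20: λ = 59 × 0.04 × 1.264 / 0.25 = 11.9, rejection about 60%

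**Step 4, simulation** (600 replicates per cell, 5% level). The autocorrelation test is a Moran-type permutation test on the pagoda proportions with three nearest neighbours. Each cell gives the result for order unrelated to location / neighbours visited in succession.

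| Prevalence over enrolment | Between-pagoda chi-square | Moran-type test |
|---|---|---|
| 0.50 to 0.50 | 5% / 6% | 4% / 5% |
| 0.45 to 0.55 | 15% / 12% | 6% / 19% |
| 0.40 to 0.60 | 56% / 61% | 4% / 55% |
| 0.30 to 0.60 | 97% / 97% | 5% / 79% |

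The chi-square does not depend on visiting order. The gap between its two values is simulation error: the standard error near 0.60 is √(0.6 × 0.4/600) = 0.02. The Moran-type test departs from its nominal level only when neighbouring pagodas are visited close in time.

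**The case against.** The strongest reply is that much of what would make this serious is not in the document. The enrolment months are not given, so enrolment may lie within one fairly stable season. Persistence of up to 4 months would outlast enrolment and damp week-to-week change. The number of pagodas is not stated and revisits are not excluded. Catchments may overlap in a small town, and houses are geocoded as well as pagodas. The 13 × 2 chi-square is not a planned test, and for spatial autocorrelation, which is planned, drift does no harm if visiting order is unrelated to location. Enrolment is one of seven rounds, the analyses affected are secondary or exploratory, and model terms are often left to an analysis plan.

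Most of this stands, and it limits size and certainty. Three stronger readings should be set aside:
- **That false clustering will occur.** It needs material drift, and for autocorrelation also a geographic visiting sequence. The article states neither.
- **That no model could separate place from time.** This holds for unrestricted pagoda and week effects when each pagoda has one week. A smooth time trend with house coordinates, overlapping catchments or revisits would allow partial separation, under assumptions.
- **That the seasonal estimates are mislabelled.** The article says saliva seroprevalence "will be presented as proportion representing point prevalence for each season in each year of the study", but Table 2 lists enrolment apart from the dry and wet rounds. Nothing says that enrolment supplies one of those estimates.

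The reply does not remove the confounding. The recruitment schedule is fixed in this document, and the time terms it states are too coarse to act within enrolment.

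**Conclusion.** The point holds in limited form. As written, location and calendar week are largely confounded in the enrolment round. Drift in saliva reactivity over those three months can appear as differences between neighbourhoods or as space-time clusters, and the stated year, season and season-specific climate terms do not clearly address it.

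The percentages in the working illustrate sensitivity to assumed drift with one pagoda per week. They are not the study's error rates, and no error rate was computed for the space-time scan.

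Full confounding is confined to one round of seven. Later rounds could repeat it in part if pagodas are again taken in turn within the ±28-day windows, but the article does not say that they are. The dengue seroprevalence sample size is not affected. The change is worth making because it costs little and reduces a bias that following the plan as written could produce.

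**What to change.** - **Models.** Include draw date, for example as a smooth calendar-time term, in the spatial and clustering models of SGH reactivity. This should need only the visit date, which the case report forms can be assumed to hold.
- **Rounds.** Base spatial conclusions, including the maps of IgG against entomology, on the March and August rounds. Show enrolment only as a date-adjusted sensitivity analysis, reported by draw date.
- **Follow-up scheduling.** Where feasible, vary or interleave pagoda order within each ±28-day window, so that location and date are not tied in the same way again.
- **Reporting.** State the enrolment months, the number of pagodas and the order visited, so that readers can judge how much drift was possible.

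The cost is a few sentences in the analysis section and a scheduling rule. The enrolment round contributes less to the spatial analysis, and follow-up scheduling is slightly less flexible.
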